## Abstract

The objectives of this research project are to study in patients with primary myelofibrosis (PMF) and Essential Thrombocythemia (ET); (1) the uptake patterns of ^18^FLT-PET (FLT-PET) and its value in diagnosing, staging, and treatment response monitoring of malignant hematopoiesis, (2) compare imaging findings from FLT-PET with bone marrow biopsy (standard of care), and (3) associate FLT-PET uptake patterns with genetic makeup such as JAK2 (Janus kinase 2), CALR (Calreticulin), MPL (myeloproliferative leukemia protein), Triple negative disease, and allele burden.

This trial is registered in ClinicalTrials.gov with number NCT03116542. Protocol version: Mar 2017

## Introduction

1

Positron emission tomography (PET) with fluorodeoxyglucose (^18^F-FDG) combined with computed tomography is a major tool for the diagnosis, staging, and monitoring of treatment response in clinical oncology.^[1]^ 3′-18Fluoro-3′-deoxy-L-thymidine (FLT) with PET is a surrogate for assessing noninvasively.^[2]^

Myeloproliferative Neoplasms (MPNs) are clonal hematopoietic stem disorders are characterized by high rate of effective proliferation of one or more cell lineage. MPNs exhibit overlapping syndromes that can progress to fibrotic stage or progress into acute leukemia. Preliminary results of a pilot study^[3]^ suggested that this technique (FLT-PET) could be useful to assess bone marrow (BM) activity and extramedullary hematopoiesis in patients with Myelofibrosis (MF).

The current standard of care approach for follow-up in patients with MF is based on pathological markers (peripheral blood counts and bone marrow histomorphology) and molecular markers. Bone marrow examination is considered as the gold standard diagnostic method in MF patients. It provides detailed information about cellularity, morphology of each lineage, the degree of fibrosis, and, transformation and dysplastic features. However, many patients are reluctant to go for this invasive technique which precludes precise assessment of disease activity at the desirable frequencies. Alternative noninvasive clinical techniques are still lacking.

In a recent study, Vercellino et al showed the feasibility of FLT-PET to evaluate the diagnostic value of this technique in in primary myelofibrosis where ^18^F-FLT PET appears to be a reliable and convenient technique to assess hematopoietic activity in bone marrow.^[4]^ Assessing the patterns of ^18^FLT uptake in the different subgroups of MPNs are still however needed. In this study protocol we propose to study and characterize FLT uptake patterns in PET images of early prefibrotic stages of PMF (pre-PMF) in different clinical and genetic settings, and Essential Thrombocythemia (ET).^[4]^ Specifically, we will assess the value of FLT-PET uptake patterns in diagnosis and treatment response assessment of PMF patients. We will also examine their feasibility to differentiate between early stage PMF and ET, and will correlate those with disease activity, degree of fibrosis, and early detection of acute transformation.

## Objectives

2

The objective of this study is to:

Assess the value of FLT-PET uptake patterns in the diagnosis, staging, and response to therapy monitoring of malignant hematopoiesis in patients with pre-PMF and ET diseases.Identify different patterns of uptake in patients with pre-PMF and ET in different clinical settings.Compare the values of FLT-PET in disease diagnosis, assessment of disease activity, detection of transformation, monitoring of treatment response, and grading of fibrosis to those of bone marrow biopsy (gold standard) in pre-PMF and ET.Study the ability of FLT-PET to differentiate between pre-PMF and ET.Correlate FLT-PET uptake patterns with different genetic makeup (JAK2, [calreticulin] CALR, MPL, or Triple negative disease) or allele burden in patients with pre-PMF and ET.

## Trial design

3

This is a phase-I, Diagnostic, Single Group Assignment, Open Label clinical study

## Methods: participants, interventions, and outcomes

4

### Study setting

4.1

The study will take place in the National Center for Cancer Care and Research (NCCCR) exclusively where the hematology outpatient, hematology lab, and PET/CT departments will be involved. All patients are diagnosed and/or followed in NCCCR, and all the investigators on this protocol are from NCCCR. The details of the procedure and interventions are mentioned below in the background and methods sections.

### Eligibility criteria

4.2

1.Cases fulfilling WHO2016 diagnostic criteria for PMF or ET.^[5]^2.WHO criteria for pre-PMF.

#### Major criteria

4.2.1

1.Megakaryocytic proliferation and atypia, without reticulin fibrosis > grade 1∗, accompanied by increased age-adjusted BM cellularity, granulocytic proliferation and often decreased erythropoiesis2.Not meeting the WHO criteria for *BCR-ABL1*+ CML, PV, ET, myelodysplastic syndromes, or other myeloid neoplasms3.Presence of *JAK2*, *CALR* or *MPL* mutation or in the absence of these mutations, presence of another clonal marker∗∗or absence of minor reactive BM reticulin fibrosis.

#### Minor criteria:

4.2.2

Presence of at least one of the following, confirmed in 2 consecutive determinations:

1.Anemia not attributed to a comorbid condition2.Leukocytosis >11 × 109/L3.Palpable splenomegaly4.LDH increased to above upper normal limit of institutional reference range.

### Diagnosis of pre-PMF requires meeting all 3 major criteria, and at least one minor criterion

4.3

∗∗In the absence of any of the 3 major clonal mutations, the search for the most frequent accompanying mutations (e.g. *ASXL1, EZH2, TET2, IDH1/IDH2, SRSF2, SF3B1*) are of help in determining the clonal nature of the disease

**∗∗∗**Minor (grade 1) reticulin fibrosis secondary to infection, autoimmune disorder, or other chronic inflammatory conditions, hairy cell leukemia or other lymphoid neoplasm, metastatic malignancy, or toxic (chronic) myelopathies

WHO diagnostic criteria ET Major criteria Platelet count ≥450 × 109/L Bone marrow biopsy showing proliferation mainly of the megakaryocyte lineage with increased numbers of enlarged and mature megakaryocytes with hyperlobulated nuclei. No significant increase or left shift in neutrophil granulopoiesis or erythropoiesis and very rarely minor (grade 1) increase in reticulin fibers.

Not meeting WHO criteria for BCR-ABL1+ CML, PV, PMF, myelodysplastic syndromes, or other myeloid neoplasms. Presence of JAK2, CALR, or MPL mutation Minor criterion Presence of a clonal marker or absence of evidence for reactive thrombocytosis. Diagnosis of ET requires meeting all 4 major criteria or the first 3 major criteria and the minor criterion

### Other inclusion criteria

4.4

Age 18 years old or above.Patient accept to sign inform consent.ECOG performance less than or equal 2.

## Exclusion criteria

5

1.Patient not fulfilling the inclusion criteria.2.Vulnerable groups: pregnant, minors, and prisoners will be excluded.

Bone marrow will be collected as part of the routine diagnostic work-up. No extra bone marrow material will be collected solely for the aim of the study.

### Outcomes

5.1

Primary outcome measure:

Number of patients with ≥ 50% increase in FLT uptake in the PET images compared to and at 12 months post-baseline scan in patients with PMF and ET.∘Examine the value of FLT-PET in assessing malignant hematopoiesis in patients with PMF and ET [Time Frame: 12 Months]

Secondary outcome measures:

Reduction of >50% of allele burden of different mutations (JAK-2, MPL, CALR) and its expression on FLT- PET uptake pattern 12 moths post-baseline scan.∘Correlation of different mutations (JAK-2, MPL, CALR) expression and allele burden with FLT- PET uptake patterns [Time Frame: 12 Months].

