### Sample size and recruitment

5.3

All patients will undergo static whole-body FLT PET/CT imaging at baseline in a cohort of 21 patients.

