## Methods: data collection, management, and analysis

6

All enrolled patients will undergo a baseline FLT PET/CT at baseline. All PET data will be acquired on the Siemens mCT PET/CT scanner in 3D mode. FLT-PET scans will be performed in static mode 60 minutes ± 10 minutes postinjection.

Diagnostic agent [^18^F] FLT: FLT will be synthesized by the HMC Radiochemistry Facility. The target patient activity will be 10 mCi ± 10%. The product will be required to meet all of the release acceptance criteria outlined by HMC policies for purity, sterility, endotoxin, and identity before administration.

Patient preparation and administration of FLT-PET: No specific dietary restrictions or hydration are required for FLT-PET scans. However, patients will be urged to drink plenty of water before and after the PET studies. FLT will be prepared by the HMC cyclotron Core Facility and assessed for quality control following “good manufacturing practice” criteria. For each scan, patients will receive approximately up to 10 mCi ± 10% FLT by intravenous infusion.

Whole body scan:

The baseline FLT-PET study will be performed in static mode as follows: Static FLT-PET acquisition:

Scout view and low dose CT (see below) for 2 to 3 PET FOV's (∼24 cm per FOV) will be obtained.Static PET acquisition will start at 60 min ± 10 min post-injection at 3 minutes per PET field-of-view.

All studies will be carried out on a Siemens mCT PET/CT scanner residing at the PET center at HMC, and in 3D mode.

Image analysis and interpretation details:

All FLT-PET images will be reviewed and examined by a board-certified physician who is a member of the HMC PET/CT or radiology services, and who is experienced in PET interpretation. CT, attenuation-corrected PET, and fused PET-CT images will be available and reviewed simultaneously for each patient. Interpretation of the cancer site will be based on lesion SUV, facility of radiotracer uptake, and detectability.

**Bone marrow examination**: Bone marrow biopsy will be performed as a part of routine work-up for all selected patients before the FLT-PET scan. Subjects will be categorized based on their diagnosis; ET/Prefibrotic myelofibrosis vs borderline undifferentiated, and ET vs/or Prefibrotic.

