### Statistical methods

6.2

The primary aim is to study the ability of FLT-PET in differentiating between pre-PMF and ET. The focus of the data analysis in our study is to determine the predictive value and accuracy of FLT-PET uptake in predicting diagnosis. For this purpose, we will use receiver-operating-characteristic (ROC) curves and will compute areas under curves for each parameter for its robustness in predicting diagnosis. In addition, we will create a model probability cutoff graph to choose parameters that best predict response and determine cutoffs that showed highest accuracy (sensitivity, specificity, positive, and negative predictive values of these parameters). The ROC curves provide a comprehensive and visually attractive way to summarize the accuracy of predictions. The ROC curve shows the tradeoff between sensitivity and specificity and is a better method to detect the performance of a developed test. Kruskal-Wallis will be also used in addition or to replace ROC curves depending on the final number of recruited patients and statistical conditions. A 2-sided *P* value <0.05 will be considered to be statistically significant. All statistical analyses will be done using MedCalc (Medcalc Software, Ostend, Belgium).

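### The primary outcome counts FLT-PET changes with no disease-status input, so on its own it cannot identify the value of the test that it is meant to examine

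*Protocol article*

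**What the plan says.** Outcomes (5.1) sets the primary measure as the "Number of patients with ≥ 50% increase in FLT uptake in the PET images compared to and at 12 months post-baseline scan", pooled over PMF and ET. The purpose attached to it is "Examine the value of FLT-PET in assessing malignant hematopoiesis in patients with PMF and ET". The secondary outcome in the same section relates reduction in mutant allele burden to FLT uptake pattern at 12 months.

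The design is single-arm: "This is a phase-I, Diagnostic, Single Group Assignment, Open Label clinical study". Sample size and recruitment (5.3) gives baseline imaging "in a cohort of 21 patients" and no target count or reference rate.

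Disease-side information appears in other places:
- Objectives (2) compares FLT-PET in several uses with marrow biopsy, ending with "grading of fibrosis to those of bone marrow biopsy (gold standard) in pre-PMF and ET".
- The data collection section (6) times the biopsy: "Bone marrow biopsy will be performed as a part of routine work-up for all selected patients before the FLT-PET scan".
- Data management (6.1) says that clinical, pathological and genetic data will be correlated with uptake patterns.
- Statistical methods (6.2) takes diagnosis as the reference: "The primary aim is to study the ability of FLT-PET in differentiating between pre-PMF and ET", and will "compute areas under curves for each parameter for its robustness in predicting diagnosis".

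**The concern.** The value of a test for assessing disease lies in its relation to the disease. The primary measure compares the index test with itself at two times. A patient whose uptake rises by half counts the same whether the disease progressed, stayed stable or improved, and with one group there is no control rate to set the count against.

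The main reported result would then be a proportion of patients with a rise. A reader could take a high or a low figure as evidence for or against the scan, although the figure alone cannot bear that reading. More careful analysis of the same count would not help, because the missing element is a variable and not a method.

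**Working it through.** **Inputs.** N = 21 comes from Sample size and recruitment (5.3), and the single group from Trial design (3). The outcome definition comes from Outcomes (5.1); its sentence lacks a clear comparator, and I read it as change from baseline. The protocol gives no progression rate, so 30% is an assumption for illustration. The plan states no expected count, null rate or power, so there is no figure of its own to reproduce.

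**1. Two scans of opposite worth, one distribution.** Let D = 1 if the patient progresses, with P(D = 1) = 0.30, and T = 1 if FLT rises by at least 50%.
- Scan A tracks progression perfectly, T = D. P(T = 1) = 0.30, and agreement with D is 1.00.
- Scan B is unrelated to progression and rises in 30% of patients. P(T = 1) = 0.30, and agreement with D is 0.30 × 0.30 + 0.70 × 0.70 = 0.09 + 0.49 = 0.58.

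The count is Binomial(21, 0.30) for both: mean 21 × 0.30 = 6.3, with 2.5% and 97.5% points at 2 and 11.

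**2. The result does not need a perfect scan.** With progression 30%, sensitivity 90% and specificity 90% (all assumed), P(T = 1) = 0.30 × 0.90 + 0.70 × 0.10 = 0.34. A scan that is positive in 34% of patients regardless of disease gives the same Binomial(21, 0.34). The likelihood ratio between the two is 1 at every count.

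**3. All possible tables.** For a count k and D progressors out of 21, every 2×2 table with those margins was enumerated.
- For every k from 1 to 20, with D unspecified, Youden's J (sensitivity + specificity − 1) can range from −1 to +1.
- With k = 7 and D = 7, let TP be the number of progressors who show a rise. Sensitivity is TP/7 and specificity is (14 − (7 − TP))/14. TP = 0 gives 0% and 50%; TP = 7 gives 100% and 100%. The count is 7 throughout.
- At k = 0 or k = 21 with both disease states present, J is exactly 0. At those extremes the 50% cut-off is shown not to discriminate, though FLT-PET measured in another way is not ruled out.

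**4. What the count does estimate.** It estimates a proportion. For 7 of 21 this is 33%, with an exact 95% interval of 15% to 57%.

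**5. Whether another section supplies the link.** Biopsy is placed before the FLT-PET scan, no 12-month biopsy is stated, and the Exclusion criteria section (5) rules out marrow collection solely for the study. The ROC analysis uses diagnosis as its reference and is not attached to the 12-month count. The correlation in 6.1 concerns uptake patterns in general. The secondary outcome comes closest, since it connects a disease marker with FLT at 12 months, but it does not enter the primary measure.

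**The case against.** The strongest reply is that disease information is in the plan. The secondary outcome already relates allele burden to FLT uptake at 12 months, 6.2 uses diagnosis as reference, and the Objectives name biopsy as gold standard. On this view the dispute is only about which outcome is labelled primary. Much of that stands: the point concerns the primary outcome and not the whole study, and the repair draws on what the secondary outcome already needs. It does not remove the point, because the question about value is written under the count.

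A second reply is that a descriptive primary outcome is acceptable in a phase I, single-group study of 21. That would be fair if the stated purpose were descriptive. Here the purpose is to examine value.

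The point also overlaps with the different primary aim in 6.2, but it is not the same. Even if 6.2 were rewritten to analyse this count, the count would still lack a disease-side variable.

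Two stronger readings are tempting and not supported.
- A reader might infer that every count from 0 to 21 is equally compatible with a valuable and a worthless scan. That holds only when the two have the same positive rate. At 30% progression a perfect scan gives a count of 0 with probability 0.7^21, about 0.0006. A scan showing only noise, with an assumed within-patient CV of 15%, gives 0 with probability of about 0.56. Counts can therefore differ in likelihood between particular scenarios.
- A reader might infer that noise alone would often produce a positive trial, since at that CV at least one of 21 shows a rise with probability of about 0.44. The plan nowhere treats a nonzero count as success, and it gives no CV.

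**Conclusion.** The point holds in a limited form. The primary outcome is a marginal count of index-test changes. Without cross-classification against disease status it does not identify the value of FLT-PET in assessing malignant hematopoiesis. The size is best shown by the paired example: 100% against 58% agreement with progression, with the same distribution of the count. The 30% is assumed. Another rate changes the 58% but not the conclusion, because an unrelated scan with the same positive rate always gives the same count distribution. The conclusion also rests on reading the outcome as change from baseline. It is a fault in how the outcome is defined, not an arithmetic error, and it should be corrected before the count is presented as evidence about the test.

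**What to change.** In Outcomes (5.1), define the primary measure as the association of 12-month percent change in FLT uptake with change in disease status over the same period:

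1. In mutation carriers, the rank correlation, with 95% confidence interval, of percent FLT change with change in mutant allele burden.
2. In all patients, including triple-negative disease, a cross-table of FLT rise (yes/no) against a disease-change status. Define that status before the scans are read, and base it only on clinical data that the plan compiles (6.1) and that are actually collected at 12 months. LDH and palpable spleen appear in the protocol as diagnostic criteria, not as stated 12-month assessments, so they should not be assumed available.
3. The count of patients with a rise of at least 50%, reported as description only.

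The cost is new outcome wording, a written definition of disease change and one further analysis. No scan is needed beyond those that the current outcome implies, and no additional biopsy. The drawbacks are that at most 21 patients contribute, so the association will be imprecise and must be shown with its interval, and that triple-negative patients drop out of the allele-burden correlation.

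### The primary 12-month outcome counts only rises of at least 50% in FLT uptake, so no defined outcome registers a fall, although monitoring response to therapy is an objective

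*Protocol article*

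**What the plan says.** Section 5.1 (Outcomes) gives the primary measure as "Number of patients with ≥ 50% increase in FLT uptake in the PET images", assessed 12 months after the baseline scan. The line beneath it states the purpose: "Examine the value of FLT-PET in assessing malignant hematopoiesis in patients with PMF and ET [Time Frame: 12 Months".

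The secondary measure in the same section is "Reduction of >50% of allele burden of different mutations (JAK-2, MPL, CALR") and its expression in the uptake pattern at 12 months. A further line adds "Correlation of different mutations (JAK-2, MPL, CALR) expression and allele burden with FLT- PET uptake patterns", also at 12 months.

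Section 2 (Objectives) includes "response to therapy monitoring of malignant hematopoiesis in patients with pre-PMF and ET diseases" in the first objective. The third objective again lists following treatment response, together with diagnosis, disease activity, transformation and fibrosis grade.

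Section 5.3 describes "static whole-body FLT PET/CT imaging at baseline in a cohort of 21 patients". Section 6.2 (Statistical methods) directs its ROC and Kruskal-Wallis analyses at diagnosis. It mentions cut-offs for predicting response without defining response, and it names no analysis of the 12-month change.

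**The concern.** The two 50% thresholds point in opposite directions: up for uptake, down for allele burden. The Introduction describes these diseases as "characterized by high rate of effective proliferation of one or more cell lineage" and presents FLT-PET as a measure of marrow activity. On that description, a patient responding to treatment would be expected to show lower uptake. A count of large rises gives such a patient a zero, the same score as a patient whose scan did not change.

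The headline result would then say almost nothing about response. A count near zero would be compatible both with a stable cohort and with one in which uptake fell sharply. In addition, a measurement taken on a continuous scale is reduced to one yes/no answer per patient in a cohort of 21.

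**Working it through.** **Inputs from the protocol article.** n = 21 (section 5.3); threshold of a rise of at least 50%, that is a 12-month/baseline ratio of at least 1.5 (section 5.1). The article gives no SD, event rate or precision target, so there is no planned figure to reproduce. The spread of the ratio and the share of patients crossing the cut are assumptions, shown as ranges.

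**Step 1: can the count separate response from no change?** Assume the log ratio is normal with median ratio m and log-SD s between 0.2 and 0.4. Then P(rise ≥ 50%) = 1 − Φ[(ln 1.5 − ln m)/s], and the expected count is 21 times this.

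| Median change | s = 0.2 | s = 0.3 | s = 0.4 |
|---|---|---|---|
| none (m = 1) | 0.45 | 1.85 | 3.26 |
| 25% fall (m = 0.75) | 0.01 | 0.22 | 0.87 |
| 50% fall (m = 0.5) | 0.00 | 0.00 | 0.06 |

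Example: m = 1, s = 0.4 gives (0.405 − 0)/0.4 = 1.01, P = 0.155, and 21 × 0.155 = 3.26. An observed 0/21 has an exact (Clopper-Pearson) 95% CI of 0% to 16%. The no-change expectation at s = 0.4 is 15.5%, inside that interval. So even an empty count would not distinguish a halving of uptake from no change.

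Compare a count of falls of at least 50%. With m = 0.5, half the patients cross by definition: 21 × 0.5 = 10.5. With m = 1, P = Φ(ln 0.5/s) = Φ(−0.693/s), which gives 0.01, 0.22 and 0.87 expected patients for s = 0.2, 0.3 and 0.4. The same scans therefore separate the two situations once falls are tabulated.

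**Step 2: information kept by one cut.** For a normal variable cut so that a proportion p lies beyond the threshold, the asymptotic relative efficiency is φ(z_p)²/[p(1 − p)].

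| p | Efficiency | 21 patients act like |
|---|---|---|
| 0.5 | 0.637 | 13.4 |
| 0.3 | 0.576 | 12.1 |
| 0.2 | 0.490 | 10.3 |
| 0.1 | 0.342 | 7.2 |

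**Step 3: precision of the count.** Exact 95% CIs: 2/21 (9.5%), 1.2% to 30.4%; 5/21 (23.8%), 8.2% to 47.2%.

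**Step 4: precision of the continuous alternative.** The 95% half-width for the mean log ratio is t(20) × s/√21 = 2.086 × s/4.583 = 0.455s. At s = 0.4 this is 0.182, a factor of e^0.182 = 1.20. An observed mean ratio of 0.50 would then carry a CI of 0.50/1.20 to 0.50 × 1.20, or about 0.42 to 0.60. This pools all 21 patients; intervals by diagnosis will be wider, by an amount that depends on a split the article does not give.

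**The case against.** The best defence is that the primary measure was not meant for response. Its explanatory line speaks of assessing malignant hematopoiesis, and the Introduction and Objectives also list detection of transformation, for which a rise is a plausible marker. The article never defines response on FLT-PET, so equating response with a fall is an inference. This stands as far as it goes: a rise-only count may serve progression or transformation. It still leaves response monitoring, stated in two objectives, without an outcome that could show a fall.

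Three stronger readings are tempting and are not supported.

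- A reader might infer that the study cannot examine agreement between falling allele burden and falling uptake. Section 5.1 lists a correlation of allele burden with uptake patterns, and that line cuts neither variable. It leaves room for continuous values, though it neither defines a continuous change nor alters the primary outcome.
- A reader might compound the loss by supposing that both variables are cut and cross-tabulated. No section plans such a table, so efficiency or power figures for it would describe a test that nobody specified.
- A reader might say the count can detect only very large effects. The study has a single group, and no test is named for the count, so there is no comparison for it to miss. The wide intervals partly reflect n = 21 itself.

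It can also be said that a condensed article may leave the reason for a 50% cut to the full protocol. That is accepted, and no criticism is made of the missing rationale.

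**Conclusion.** The point holds on direction. As defined, the primary outcome gives the same score to a halving of uptake and to no change, and no other defined outcome captures a fall. This follows from sections 2 and 5.1 alone and needs no distributional assumption. Its relevance to response does rest on reading response as a fall in a proliferation tracer, which the Introduction makes reasonable but the article does not state.

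The loss from a single cut is real but secondary. Its size (64%, 49% or 34% of the information kept) assumes a normal change and crossing proportions of 50%, 20% or 10%; the expected counts assume a log-normal ratio with log-SD 0.2 to 0.4. The loss applies to the outcome as defined, not to every analysis in the plan: the ROC and Kruskal-Wallis analyses can use uncut uptake values. No stated figure is shown to be wrong. The change is worth making because it is cheap.

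**What to change.** 1. Define the 12-month outcome as the log ratio of 12-month to baseline uptake in one SUV measure, with measure and region named in advance. Report the mean change with a 95% CI by diagnosis.
2. Specify that the correlation already listed in section 5.1 uses continuous uptake change and continuous allele-burden change, in patients with a baseline mutation. Triple-negative patients have no JAK2, CALR or MPL burden to change.
3. Keep the 50% counts as descriptive and tabulate falls as well as rises. This serves either reading of what the count is for.

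The cost is wording, and the simple count is no longer the headline. The fix needs no measurement beyond the 12-month scan and repeat allele-burden assay that the stated outcomes already require. However, sections 5.3 and 6 describe only the baseline scan, so they must be reconciled with section 5.1 for any version of this outcome to be obtainable.
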